# Cognitive Enhancement Therapy vs social skills training in schizophrenia: a cluster randomized comparative effectiveness evaluation

**DOI:** 10.1186/s12888-022-04149-x

**Published:** 2022-09-01

**Keywords:** Schizophrenia, Social skills training, Cognitive enhancement therapy, Cognitive remediation, Community functioning, Cluster randomized controlled trial, Psychosocial rehabilitation, Neurocognition, Social cognition

## Abstract

**Background:**

Schizophrenia and related disorders are highly disabling and create substantial burdens for families, communities, and health care systems. Although pharmacological treatments can often lessen the psychotic symptoms that are a hallmark of schizophrenia, they do not lessen the social and cognitive deficits that create the greatest impediments to community engagement and functional recovery. This study builds on prior research on psychosocial rehabilitation by comparing the effectiveness of two treatments demonstrated as efficacious in improving social and community functioning, Cognitive Enhancement Therapy (CET) and a version of Social Skills Training (HOPES/SST).

**Methods:**

The study uses a randomized cluster design in which a pair of clinicians at community- and hospital-based mental service centers deliver either CET or HOPES to at least one group of 6-8 eligible clients for 12 months. Clinicians are trained and then supervised weekly, with ongoing process measurement of treatment fidelity, attendance, satisfaction, and retention, and use of other services. Measures administered at baseline and at 6 and 12 months while in treatment, and then at 18 and 24 months after treatment include social adjustment, quality of life, social skills, positive and negative symptoms, and neuro- and social cognition. We hypothesize that CET will be associated with greater improvements than SST in both the primary outcome of community functioning and the secondary outcomes of neuro- and social cognition and social skills. Secondarily, we hypothesize that more cognitive impairment at baseline and younger age will predict more benefit from CET compared to HOPES.

**Discussion:**

Resource shortages endemic in mental health services and exacerbated by the pandemic highlight the importance of identifying the most effective approach to improving social and community functioning. We aim to improve understanding of the impact of two efficacious psychosocial treatments and to improve clinicians’ ability to refer to both treatments the individuals who are most likely to benefit from them. We expect the result to be programmatic improvements that improve the magnitude and durability of gains in community functioning.

**Trial registration:**

ClinicalTrial.gov NCT04321759, registered March 25, 2020.

## Background

Schizophrenia (SZ) and related disorders occur in between .4-1% of the population across the world—about 2 million individuals in the United States, with 100,000 new cases diagnosed each year. They are highly disabling, create substantial burdens for their families and communities [1–3], and cost the US more than $100 billion annually [4, 5]. Although psychotic symptoms are the most florid manifestations of SZ and related psychotic disorders [6], associated impairments in social and cognitive functioning are the most disabling features of this diagnosis [7, 8]. While pharmacological treatments can lessen positive symptoms for many individuals [9–11], they do not improve social or cognitive functioning [7, 12–18]. As many as two-thirds of people with SZ have social skills impairments [19, 20], over 90% are impaired in one cognitive domain, and 75% are impaired in at least two domains [21–24]. Impaired cognitive and social cognitive functioning are also rate-limiting factors in response to psychosocial treatment and constrain prospects for community engagement and functional recovery [19, 20, 23, 25–30].

An array of psychosocial programs to improve social skills and cognitive functioning have been developed in recent decades. Social skills training (SST) is a common approach to improving social functioning, most often provided in a group format, aimed at teaching more effective interpersonal skills. Skills are taught based on the systematic application of social learning theory, and include the following steps: breaking complex skills down into smaller steps or components, demonstrating (modeling) the skill for participants in a role play, engaging each participant in practicing the skill in role plays with each one followed by positive feedback and suggestions for improvement, collaboratively developing home assignments for participants to practice the skills on their own, and in vivo community trips to practice the skill. Considerable evidence supports the efficacy of SST in improving social and community functioning as well as reducing negative symptoms [23, 24].

Cognitive remediation (CR) programs take a different approach to improving functioning, with a focus on enhancing cognition through practice of computer cognitive exercises, coaching in strategies designed to improve performance on the cognitive exercises, and teaching self-management (or compensatory) skills to improve cognition in day-to-day situations. Although most cognitive remediation programs have produced moderate gains in overall cognitive performance [31, 32], by themselves they have had limited lasting, positive effects on more ecologically valid abilities that shape community functioning [33]. It is when cognitive remediation programs also include strategic training and more comprehensive integration with other psychosocial interventions that they have more effects on functioning [32, 34–37]. Meta-analyses suggest that such comprehensive programs have stronger effects on community functioning than either treatment administered separately [37, 38]. However, these more comprehensive treatments have not been compared directly to traditional SST programs that do not include a CR component.

The Patient-Centered Outcomes Research Institute (PCORI) funded Project SUCCESS, Schizophrenia: Understanding and Comparing Cognitive Enhancement and Social Skills training to fill this knowledge gap and thus inform the treatment decisions of clinicians, individuals with SZ, and other stakeholders. Meta-analyses and independent randomized controlled trials (RCTs) of comprehensive CR treatment, including Cognitive Enhancement Therapy (the one we will provide) indicate moderate to large effect sizes (Cohen’s *d* between .4- 1.0, averaging .8) on cognition, social cognition, and community functioning in both early course and multi-episode patients with SZ (see Table 1) [21, 22, 32, 37, 39, 43]. By comparison, meta-analyses of RCTs testing SST treatments show small to moderate effect sizes (about .2-.5) on social skills and community functioning [23, 24, 44]. Improvements in community functioning are sustained after both treatments for at least 1-2 years [41, 42, 45–48].

**Table 1 Tab1:** Effect Sizes for RCTs of CET and SST in Schizophrenia

Study	Design	Interventions	Effect sizes
Eack et al. 2009 [39]	RCT	CET vs enriched supportive therapy	.82^a^, 1.53^b^ social adjustment (SAS-II); 1.08^a^, 1.55^b^ social cognition
Wojtalik et al. 2021 [40]	RCT	CET vs enriched supportive therapy	.74^a^ role functioning
Bartels et al. 2014 [41]; Mueser et al. 2010 [42]	RCT	HOPES (SST) vs TAU	.20^a^, .29^b^,.08^c^ social functioning (SBS) .25^a^, .32^b^, .25^c^ independent living (ILSS) .44^a^, .37^b^, .26^c^ community functioning (Multnomah CAS) .54 ^a^, .53^b^, .27^c^ negative symptoms (SANS) .51 ^a^, .45^b^, .27^c^ social competence (UPSA)
Kurtz et al. 2008 [23]	Meta-analysis of RCTs	SST vs TAU	.47 negative symptoms .41 psychosocial functioning
Turner et al. 2018 [24]	Meta-analysis of RCTs	SST vs TAU	.32 (PANSS) .19 (negative symptoms) .41 (social competence)

^a^12-month effect sizes, ^b^24-month effect sizes; ^c^36-month effect sizes

## Methods

### Aims and hypotheses

Our primary study aim is to test the hypothesis *that CET will be associated with greater improvements than SST* in both the primary outcome—community functioning—and the secondary outcomes of neuro- and social cognition and social skills (see Fig. 1).

**Fig. 1 Fig1:**
[figure not shown]
Causal Model

Our secondary aim is to explore the differential effectiveness of the two interventions by baseline cognitive functioning and age. Because integrated treatment programs like CET were designed to reduce the moderating effects of impaired cognition on response to social skills training [20, 23], we predicted that *poorer baseline cognitive functioning* will be associated with *greater treatment response* for patients who receive CET as compared to those who receive SST (which doesn’t seek to increase cognitive functioning) [32, 37, 49–56]. Given that the younger brain retains neuroplastic reserves that may make it uniquely capable of benefiting from cognitive remediation [57–59], we also predicted that younger participants would benefit more from CET than older ones, while the same interaction with age would not occur for SST recipients [60–62]. Variation across our treatment delivery sites (approximately 24) in treatment dose may also influence the effectiveness of both interventions, with individuals attending more treatment sessions—even when it is due to challenges at the site rather than orientations of the participants—potentially benefiting more from the treatment.

### Trial design

Project SUCCESS is a comparative effectiveness trial of Cognitive Enhancement Therapy (CET), a combined treatment offering both CR and features designed to improve social functioning, with Helping Ourselves Pursue and Experience Success (HOPES), a treatment that offers only SST. The study uses a cluster-randomized design to allocate participating treatment sites to provide either CET or HOPES in groups of 6-8 eligible participants for 12 months of treatment, with post-treatment assessments of functioning conducted up to 12 months post-treatment. Most sites will offer two successive treatment groups.

### Study setting and sample

Treatment sites are approximately 24 community mental health centers and hospital outpatient clinics in Massachusetts and eight other states that offer programs for individuals with schizophrenia-spectrum disorders (final list on project website, project-success.net). These sites have been paired by geographic proximity, organizational type, and by race and ethnic proportions in the local community and then randomly assigned to the two study arms, so that the number of participants per arm is approximately equal and the distribution of sites is comparable geographically and unbiased with respect to participant and site characteristics.

Cluster randomization was used to reduce challenges created by the group-based nature of both treatments. We also had several other reasons to reject person-level randomization: increased resources required by participating sites to train two sets of clinicians to implement CET and SST, potential cross-contamination of the two interventions offered within the same setting, and slower accrual of groups in each treatment due to randomization to two different programs.

### Study interventions

*Cognitive Enhancement Therapy* is a comprehensive cognitive remediation program designed to maximize gains in social functioning by integrating computer-based training to enhance neurocognition with group-based exercises to improve social cognition [22, 43, 45, 57]. CET facilitates the development of adult social-cognitive milestones (e.g., perspective-taking, social context appraisal) by shifting thinking from reliance on effortful, serial processing to a “gistful” and spontaneous abstraction of social themes. All procedures are described in a step-by-step manual followed by CET trainers [45]. CET’s group-based exercises are delivered for 1.5 hours each week in a group of 6-8 participants led by two clinicians. During each of three modules (basic concepts, social cognition, CET applications), the group focuses on acquisition of adult social milestones in perspective-taking, social context appraisal, and other aspects of social functioning, with psychoeducational lectures on topics ranging from the neurobiology of schizophrenia to the concept of self-defeating thinking, homework assignments, and in-group exercises. CET’s computer-based training is supervised by a clinician who meets weekly for one hour with a pair of participants who make progress on an attention, memory, or problem-solving exercise in each session. The paired participants take turns practicing exercises on a computer, providing encouragement and advice to each other, as the clinician provides strategy coaching and support.

*Social Skills Training*: HOPES is a manualized SST rehabilitation program that is delivered over a 12-month period, with weekly group skills classes and monthly community practice trips and engagement of natural supports to facilitate skill use in real-world situations. HOPES classes are conducted using the principles of SST (modeling, role playing, positive and corrective feedback, in vivo assignments), some of it adapted from the Bellack et al. [63] curriculum. The curriculum is organized into eight topic areas or “modules”: Living Well in the Community, Communicating Effectively, Making and Keeping Friends, Making the Most of Leisure Time, Using Medications Effectively, Healthy Living, Intimacy and Dating, and Making the Most of a Doctor’s Visit. Each module includes 6–8 component skills, with one skill covered each week. HOPES is standardized in a manual and a participant workbook with handouts for each skill [48].

Two modifications have been made in the interventions and accompanying manuals to adapt CET and HOPES for the unique needs of this multi-site comparative effectiveness study.12-month intervention

Although the early studies of CET provided treatment for 24 or 18 months, CET has been adapted to be delivered as a 12-month intervention to enhance feasibility of delivery; it has been shown to be efficacious even when limited to 9 months (effect size of .74 for role functioning after 9 months of CET) [40]. Most SST programs are 6-9 months in length [24], but HOPES was designed as a 12-month intervention. We offer both CET and SST (HOPES) for 12 months to enhance the likelihood that participants will complete the entire program while allowing recruitment of new cohorts, and to standardize the length of treatment across groups. Evidence supports the effectiveness of both interventions by 12 months of treatment, with durability of effects at one-year follow-up for both CET [45, 46] and SST [42]—including for HOPES [41].

For CET, participants will be engaged in both the neurocognitive training and group-based social cognition training concurrently, upon enrollment. Although the CR component of CET has typically been initiated 3 months prior to the start of the group therapy sessions, we have found that sequential timing of CR exercises and group interventions is both impractical and unnecessary. Additionally, increasing evidence suggests that near-term transfer (immediate improvement in a test situation) of skills learned in cognitive remediation is likely to occur simultaneously with generalization to daily tasks and improve long-term transfer [58, 64, 65]. This has proven to be successful both in our own research programs and related implementation efforts [66]. This strategy also assures similar treatment lengths, without limiting our ability to answer the main study questions. We have developed a supplement to the CET manual describing adaptations for the 12-month intervention.2)Replacement of dropouts in first month (partial rolling admission) for CET groups

HOPES typically uses an open enrollment format where participants can join the group at any point in the curriculum, which is taught on a revolving basis for as long as needed with the last module followed by the first module, and then remain in the program for a full year. An open enrollment format can minimize the time participants have to wait to join a new group, and is feasible in HOPES because the skills taught in the different modules are not cumulative, and thus can be learned in any order. Fully open enrollment is not feasible in CET, since some of the later modules (such as CET application to everyday life situations) require prior practice of the cognitive skills. The standard CET approach instead has been to allow replacement of dropouts in the first month of treatment, with some preliminary coaching of those who enter in weeks 2-4. We therefore have also imposed a first-month limit for enrollment to standardize this aspect of both treatments.

#### Adaptations for the COVID-19 pandemic

The COVID-19 pandemic required an abrupt and massive shift of community mental health services to telehealth modes of service delivery. Prior research indicated the potential for remote delivery of psychosocial interventions, but mostly in relation to individual therapy rather than group-based treatments [67–76]. We adapted our intervention delivery and research procedures to maintain equivalent service experiences and assessment protocols even when services and assessments must be delivered remotely. Monthly group community trips in HOPES were changed to virtual monthly meetings of each participant with an identified support person. Virtual group (and individual) sessions in both interventions and computer sessions in CET were offered on tablets or laptops. We have tested these telehealth adaptations for acceptability and feasibility in a 3-month pilot study at four service sites, two of which were assigned to CET and two to HOPES, with one in each condition delivering the intervention via telehealth and the other delivering the intervention in-person, as allowed by site policy and with adherence to site-specific public health requirements (e.g., social distancing, masking). Data on treatment enrollment, retention, participant satisfaction, and treatment fidelity indicate the feasibility and acceptability of the telehealth approach.

### Eligibility and randomization

Potential participants are eligible if the referring clinician reports a DSM-5 diagnosis of schizophrenia, schizoaffective disorder, or schizophreniform disorder that is confirmed by a Mini International Neuropsychiatric Interview (MINI) for Psychotic Disorders Studies [77] administered via video conference by the project research coordinator. Participants must also be 18-65 years of age and have an estimated premorbid IQ > 70 (determined with the Wechsler Test of Adult Reading) and have no known organic neurological disease or intellectual disability (DSM-5). Prior to assessment, on-site research assistants review the project with potential participants and invite their participation if they sign a site- and treatment-specific Informed Consent Form.

Assessments of symptom severity, social cognition, and community functioning will be conducted via video conference by trained research assistants at the coordinating site, Beth Israel Deaconess Medical Center (BIDMC), who are blind to treatment condition. Treatment fidelity will be assessed by coding at least 10 recorded group therapy sessions each year for each treatment site, with 6 sessions in the first 3 months used for feedback and training and 4 or more at random intervals after that. Site research assistants will record participant attendance and engagement during group sessions.

### Sample size and power

We expect that each treatment site will enroll on average about 16 participants, yielding a total of 378 participants (see Fig. 2). For all power analyses conducted, based on previous experience, we assumed 20% attrition by 12 months. We further assumed four assessment points (baseline, 6-, 12-, 18- and, for 75% of the sample, 24-month), an alpha level of 0.05, a two-tailed test, with a cross-time correlation of 0.5. We will minimize treatment dropout by reaching out to participants whenever they miss treatment sessions (through the site RA) and by providing makeup sessions (through the site clinicians) that allow those who have missed up to eight sessions to reengage in the treatment without missing content. We will minimize attrition from the research procedures by identifying multiple contact persons when enrolling each participant and by using multiple forms of outreach when a participant is not available for scheduling an assessment or misses a scheduled assessment. Based on our prior experience conducting clinical trials evaluating CET and HOPES (reviewed above), combined with our methods for minimizing attrition, we also believe it is realistic to estimate that the attrition rate for the 1-year durability follow-up will not exceed 20%. However, to be conservative we have estimated our power to detect significant differences between the groups based on a 25% attrition rate.

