**Fig. 2 Fig2:**
[figure not shown]
CONSORT 2010 Flow Diagram (Anticipated Numbers)

To estimate effect sizes, we compared effect sizes of CET and SST/HOPES from our own data and the SST literature using randomized controlled designs in schizophrenia, bearing in mind the diversity of design and treatment length issues (see Table 1). Given that CET is a composite intervention that includes both cognition, social cognition and social skills interventions, the effect sizes are not surprisingly higher (from .7 after 1 year to > 1.0 after 2 years); SST effect sizes are mostly under .4 in meta-analyses of SST of lengths from 3 weeks to 2 years (and in the HOPES trial did not consistently lessen for one or even 2 years after active treatment). Based on the available studies outlined in the table, we estimated effect sizes of 0.34 (for ICC due to clustering at site level = .01) and 0.37 (for ICC = .02), which justifies our proposed full sample size. With 4 assessments for the full and 5 assessments for three-fourths of the sample, our durability assessment is only somewhat less powerful, with medium effect sizes (from 0.41 to 0.49).

*Accounting for clustering and correlated data.* There are multiple forms of clustering due to participants being nested in sites and repeated observations being nested in participants. Therapeutic groups within a site can also be considered as another level of clustering, but because there are no more than 3 therapeutic groups at any site and they are expected to be led by the same clinicians at the site, we expect little between-therapeutic group heterogeneity within sites and so this level of clustering is unlikely to affect estimates. Nonetheless, we conducted two sets of power analyses, with and without considering therapeutic groups as another level of clustering.

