We first only consider clustering effects due to sites and repeated measurement and handle clustering effects as follows: for the correlated nature of data due to repeated measurement, we assumed within-person cross-time correlation to be 0.50 and incorporated this correlation into both analytic modeling procedures (mixed-effects model with random effects) and power calculations. To account for site level clustering effects, we adjusted for sample sizes of 378 individuals by assuming a range of ICC values: 0.01, 0.02 and 0.05. We note the literature reports that in public health and medicine, ICCs in group- or cluster-randomized trials are often small, usually ranging from 0.01 - 0.05 (https://researchmethodsresources.nih.gov/FAQs.aspx). Some statisticians have stated that values of ICCs are usually between 0.01 and 0.02 in cluster randomized clinical studies [78, 79]. Given the multi-determined nature of our health-related outcomes, we believe that the effects due to clustering by site in our study will be small, and thus we adjusted our sample size and power calculations based on two scenarios: assuming an ICC of 0.01 and an ICC of 0.02. After adjustment, our original sample size of 378 reduced to an effective sample size (ESS) of 318 (for an ICC of 0.01) and 274 (for an ICC of 0.02), respectively. Second, for the 3-level clustering effects adjustment, we took account of the 51 therapeutic groups (approximating) as another level of clustering and assumed an ICC due to therapeutic group of 0.01, and adjusted sample sizes by both site and therapeutic group down to 302 and 252, respectively.

#### Power for aim 1

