Power analyses for Aim 1 were conducted using Diggle et al. [80] and Lu et al.’s [81] approaches implemented in the LongPower package [82] in R statistical software (version 3.52). Power calculations were conducted to determine minimum detectable differences between arms (CET vs. SST) in changes over time on the primary outcomes. The outcomes for primary hypotheses in Aim 1 are continuous. To detect significantly more improvement for participants in CET than SST with 80% power in the 2-level analysis, the adjusted sample size of N of 318 (with 20% attrition by 12 months) will detect a minimum effect size of 0.34, and the adjusted N of 274 will detect a minimum effect size of 0.37, respectively. Both detectable effect sizes are between small and medium according to Cohen’s d metric for effect size (0.2 = small, 0.5 = medium and 0.8 = large). For the 3-level analysis that includes adjustment for clustering at the therapeutic group level and the adjusted sample sizes of 302 and 252 (everything else is the same), the minimum effect sizes that can be detected are 0.35 and 0.38, respectively.

The full sample of 378 at baseline (thus ICC adjusted sample sizes of 318 and 274) will have 4 assessments (baseline, 6-, 12 and 18 months), but we will also collect data for 284 participants (75% of the original sample of 378) for one extra time point (baseline, 6-, 12-, 18 and 24 months) (thus an ICC adjusted effective sample size for *N* = 284 participants becomes 250—for an ICC of 0.01—and 222—for an ICC of 0.02—respectively, and so the detectable effect sizes with *N* = 250 and 222 with 20% attrition are 0.38 and 0.40, respectively. For the analysis with 3-level clustering (both site and therapeutic group, as well as participants over time), the adjusted sample sizes become *N* = 240 and 208 and the detectable effect sizes with 20% attrition are 0.39 and 0.42, respectively.

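### The power section gives two attrition rates, two durability ranges (0.41–0.49 and 0.38–0.42) and an ICC of 0.05 with no result, and these must be reconciled

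*Protocol article*

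**What the plan says.** All of this stands in the protocol article, from Sample size and power to Power for aim 1.

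- **Attrition.** The opening paragraph of Sample size and power sets 20% loss by 12 months for all power analyses. It expects loss at the one-year durability follow-up not to exceed 20%. It closes: "to be conservative we have estimated our power to detect significant differences between the groups based on a 25% attrition rate".
- **Durability, first statement.** The text after Fig. 2, on the sample with four assessments for everyone and five for three quarters, says "our durability assessment is only somewhat less powerful, with medium effect sizes (from 0.41 to 0.49").
- **Durability, second statement.** Power for aim 1 takes the 284 participants with a 24-month visit. For effective N 250 and 222 (site clustering only) it reports "222 with 20% attrition are 0.38 and 0.40, respectively". For 240 and 208 (site and therapeutic group) it reports "detectable effect sizes with 20% attrition are 0.39 and 0.42, respectively".
- **ICC.** The clustering paragraphs say that the 378 was adjusted "by assuming a range of ICC values: 0.01, 0.02 and 0.05". They then argue that site effects should be small and go on with 0.01 and 0.02 only.
- **Other inputs.** "an alpha level of 0.05, a two-tailed test, with a cross-time correlation of 0.5", and detection "with 80% power in the 2-level analysis".

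**The concern.** A reader cannot tell which calculation the trial stands behind. The attrition rate described as conservative is attached to no result. Three of the four itemised 24-month effects lie below the durability range given earlier, and none comes near its upper end of 0.49. The least favourable ICC is announced and then disappears.

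The article uses detectable effects of 0.34 and 0.37 to justify the sample size, and its Discussion calls the trial well powered. If the supporting figures come from different sets of assumptions, neither statement can be checked from the text.

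**Working it through.** **Inputs from the article.** Two-sided alpha 0.05, 80% power, within-person correlation 0.5, arms about equal ("so that the number of participants per arm is approximately equal"), 378 participants, about 24 sites, about 16 per site, 284 with a 24-month visit, 51 therapeutic groups, group ICC 0.01.

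**Assumptions made here.** Compound symmetry; loss builds linearly to the stated rate at the last visit; normal approximation with no correction for the small number of sites.

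**Formulas.**
- Effective N = N / (1 + (m − 1) × ICC), with m participants per site.
- Detectable effect d = (1.960 + 0.842) × √(4v / effective N). Here v is the variance factor of the last-visit mean in a mixed model. It is the last diagonal element of the inverse of Σⱼ (rⱼ − rⱼ₊₁) Rⱼ⁻¹, with rⱼ the proportion retained at visit j and Rⱼ the correlation matrix of the first j visits.
- v = 1.169 for four visits at 20% loss, 1.163 for five visits at 20%, and 1.217 for five visits at 25%.
- Cross-check on completers only: d = 2.802 × √(4 / (effective N × (1 − loss))).

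**1. The article's itemised figures, at 20% loss**

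| Effective N | Stated | Recalculated |
|---|---|---|
| 318 / 274 | 0.34 / 0.37 | 0.340 / 0.366 |
| 302 / 252 | 0.35 / 0.38 | 0.349 / 0.382 |
| 250 / 222 | 0.38 / 0.40 | 0.382 / 0.406 |
| 240 / 208 | 0.39 / 0.42 | 0.390 / 0.419 |

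All agree to within 0.01, so these results do use 20%.

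**2. The 24-month figures at 25% loss.** Effective N 250, 222, 240 and 208 give 0.391, 0.415, 0.399 and 0.429. Each rises by about 0.01. The effects stated in the article would then have about 77–78% power instead of 80%.

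**3. Can 0.41–0.49 be reached?**
- At 20% loss and ICC 0.01–0.02, the mixed-model formula spans 0.38–0.42 and the completer formula 0.40–0.43.
- At 25% loss and the same ICCs, they span 0.39–0.43 and 0.41–0.45.
- On the completer formula, 0.49 needs 4 × (2.802 / 0.49)² ≈ 131 completers. That is an effective N of about 163 at 20% loss or 174 at 25%. The smallest stated effective N is 208.
- An ICC of 0.05 gives an effective N of that order: 284 / (1 + 14 × 0.05) = 167 with 15 per site. At 25% loss the effect is then 0.48 (mixed model) or 0.50 (completers). Adding group ICC 0.01 with 7.4 per group (378 / 51) gives 284 / 1.764 = 161, and 0.49 or 0.51.
- For 25% loss and ICC 0.01–0.05 the full span is therefore about 0.39–0.49 or 0.41–0.51. Each formula matches one end of the article's range, and neither matches both.

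**4. Cluster size behind the effective N.** With 16 per site, 378 gives 378 / 1.15 = 329 and 378 / 1.30 = 291, not the stated 318 and 274. With 20 per site it gives 378 / 1.19 = 317.6 and 378 / 1.38 = 273.9. The stated 250 and 222 match 284 with 15 per site (249.1 and 221.9).

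**5. Main comparison at ICC 0.05, 20% loss**

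| Cluster size | Effective N | Detectable effect | Power for 0.34 |
|---|---|---|---|
| 16 per site (stated) | 378 / 1.75 = 216 | 0.41 | 64% |
| 24 sites (15.75 per site) | 378 / 1.7375 = 218 | 0.41 | 64% |
| 20 per site (implied by 318 and 274) | 378 / 1.95 = 194 | 0.43 | 59% |

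**The case against.** The article gives a reason for narrowing the ICC. It cites literature that places values in cluster randomized clinical studies mostly at 0.01–0.02, and it appeals to the many determinants of its outcomes. It says openly that two scenarios were carried forward. This stands: whether to power for 0.05 is a design judgement, and the 64% and 59% figures belong to a scenario that the authors argued against. What remains is that three ICCs are listed and results are given for two.

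The attrition discrepancy is also numerically small, about 0.01 in each detectable effect. That stands too.

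The two durability statements might describe different samples. The first speaks of the whole sample with mixed follow-up, the second of the 284 alone. Identity is indeed not stated. But a larger, mixed sample would not be expected to have larger detectable effects than its 24-month subset under the same assumptions, so the conflict is not removed.

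A reader might infer that 0.41–0.49 was produced by 25% attrition with ICC up to 0.05, and that two versions of the calculation were merged. The documents do not support that as fact. They give no derivation, no single formula above returns both ends, and other inputs also come close. For example, two successive losses of 20% (64% retained) with effective N 208 give 0.486 on the completer formula. A reader might also infer that the less favourable ICC was left out to flatter the result; the stated reason for narrowing speaks against that.

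**Conclusion.** The contradictions stand on the face of the text: 20% against 25% attrition, 0.41–0.49 against 0.38–0.42 for durability, and an ICC of 0.05 announced without a result. The itemised figures are internally sound at 20%. The range 0.41–0.49 does not follow from the stated 20% and ICC 0.01–0.02, and its origin is unknown; 25% attrition with an ICC near 0.05 is a possible, unproven explanation.

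The attrition choice alone changes little. The ICC and the unstated cluster size change more: at ICC 0.05 the main detectable effect is 0.41–0.43 and power for 0.34 is 59–64%, depending on whether 16 or about 20 per site is used. These figures rest on compound symmetry, linear loss and a normal approximation. Neither the planned sample size nor the analysis is shown to be wrong; what fails is the account of what the trial can detect. It should be corrected.

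**What to change.** 1. State one attrition rate and its time horizon. The present 20% is tied to 12 months, whereas the primary test runs to month 18 and durability to month 24. Make every figure match. If 25% is kept, the 24-month detectable effects become about 0.39 and 0.41 (site only) and 0.40 and 0.43 (site and group), under linear loss to the last visit.
2. Keep one durability range. Delete the other, or show its inputs.
3. Report ICC 0.05 as a labelled sensitivity case, or take it off the list.
4. State the number of sites and the cluster size behind each effective N, since 318 and 274 do not follow from 16 per site.

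One table would cover all four: 18 and 24 months, ICC 0.01, 0.02 and (if kept) 0.05, at the chosen attrition rate. The cost is a recalculation and a text change, with some detectable effects slightly less favourable. No change to design or conduct is needed.
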